## Abstract

Parkinson’s disease (PD) is a progressive neurological disorder that often leads to gait impairments and an increased risk of falls, negatively impacting quality of life. Inertial-based wearables have extended gait evaluation beyond clinical settings, but their technical integration and general accessibility hinder widespread adoption. Smartphones, equipped with inertial sensors, present a scalable approach for gait assessment and retraining/rehabilitation. Auditory cueing, specifically music, has shown promise to retrain gait, yet its use and uptake is often limited by a lack of personalisation. This paper outlines an exploratory and experimental protocol to evaluate CuePD, a smartphone application/app that delivers near real-time gait assessment and personalised auditory cues (including music) for gait retraining in people with PD (PwPD). The protocol characterises beneficial and non-beneficial responses to different cueing strategies and presents separate analysis for the technical validation and gait response outcomes to reduce interpretive ambiguity between measurement performance and behavioural effects. Specifically, the protocol presents: 1) validation of CuePD’s spatio-temporal gait characteristics in a controlled laboratory setting; 2) process to understand the usefulness of various auditory cues (metronome beats, instrumental music, and vocal music) to improve gait stability (i.e., increase gait speed and stride length while reducing gait variability); 3) evaluation of acceptance and preference of PwPD for personalised music cues; and 4) relationship between PwPD's musicality and their ability to adhere to auditory cues. Findings from the study will inform the suitability of gait retraining via smartphone-based app technology, personalised to the individual. Personalisation (gait characteristics and music) may potentially encourage long-term engagement for gait retraining which could lead to reduce falls and improved quality of life for PwPD. By explicitly accounting for individual variability, this protocol aims to clarify for whom and under what conditions auditory cueing is appropriate. Future work should systematically evaluate this approach as responses to auditory and/or music-based cueing in PwPD are heterogeneous with possible neutral or adverse effects, e.g., cognitive overload or exacerbation of freezing. This trial is registered at ClinicalTrials.gov (NCT06941779).

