#### Walking/gait tasks.

Participants will choose from a selection of music tracks that span genres including pop, rock, R&B, and country. All walks will be 1-minute in duration in a continuous 25m loop, including two 8.5m straight segments and two 4m turns, Fig 3. Walk #1 will be at the participant’s natural walking pace to calculate a baseline cadence, i.e., a walk with no cueing (NC). Walks #2, #4, and #6 will be cued, with external auditory stimuli (BPM set at +10% of baseline cadence) which are metronome (Me), instrumental music (IM), and vocal music (VM). Participants will be assigned to one of three counterbalanced cue sequences for Walks #2, #4, and #6. For example, the first participant enrolled to the study follows Sequence 1, the second follows Sequence 2, the third follows Sequence 3, and the fourth cycles back to Sequence 1, etc.

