**Fig 3 pone.0346508.g003:**
[figure not shown]
25m walking loop consisting of two straight and two curve sections.

Following Walks #2 and #4, a two-part washout (WO1 and WO2) will be implemented to minimise any potential carryover effects from the previous auditory cue. Part 1 (of WO1 and WO2) will involve participants sitting and counting backwards in their heads from 30 to 0 in increments of 1 to disengage any psychological responses triggered by the cueing modality [72]. Part 2 (of WO1 and WO2) will consist of a 1-minute walk at the participant’s natural pace, to further reset their gait but also to assess whether any carryover effect remains before the next cue begins. This approach ensures each cue’s effects are evaluated independently of preceding sequences:

Sequence 1–20 participants: NC, Me, WO1, IM, WO2, and VM.Sequence 2–20 participants: NC, IM, WO1, VM, WO2, and Me.Sequence 3–20 participants: NC, VM, WO1, Me, WO2, and IM.

Accordingly, the complete sequence consists of (Fig 4):

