A two-way mixed ANOVA will be used to assesses the effects of cueing modality and walk order on outcomes, i.e., cadence, gait speed, stride length, and CV_stride-time_. Comparable to the referenced PD study, cueing modality will be modelled as a within-subject factor, while walk order as a between-subject factor to account for potential sequence effects. For each outcome, within-participant changes from baseline will be calculated using cue-specific difference scores. To account for differences in scale and statistical distribution among the outcomes, change scores will be computed using Equations (30)-(31):

Percentage change of gait speed and stride length from baseline, calculated as:

$$\%\Delta =\frac{\text{Cue Value}-\text{Baseline Value}}{\text{Baseline Value}}\times \text{1}\text{0}\text{0}$$
(30)

In contrast,${\text{ CV}}_{\text{stride}-\text{time}}$, a dimensionless ratio-based variable that may have a skewed distribution, change will be computed using the natural log-ratio of cue value to baseline:

$$\Delta_{log}=\text{log}\left(\text{Cue Value}+\in \right)-\text{log}\left(\text{Baseline Value}+\in \right)$$
(31)

where 𝜖 is a small constant to avoid the logarithm of zero. This transformation was chosen as ${\text{CV}}_{\text{stride}-\text{time}}$ is a ratio-based measure that can be highly skewed and exhibit unequal variances across conditions. Applying the *log* transformation to change scores helps to normalise the distribution and stabilise the variance, thereby supporting more reliable statistical comparisons of cueing effects on ${\text{CV}}_{\text{stride}-\text{time}}$ in this within-subjects design. Post-hoc comparisons between cueing modalities will be conducted using paired t-tests, with Bonferroni correction applied to account for multiple comparisons. Effect sizes will be reported using Cohen’s d.

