### Primary objectives: Validity and evaluating the effects of personalised auditory cues on gait

The impact each personalised auditory cue has on participants’ stride length, gait speed, and${\text{ CV}}_{\text{stride}-\text{time}}$ are a significant exploratory interest. These metrics, in particular${\text{ CV}}_{\text{stride}-\text{time}}$, where a decrease is known to reduce the risk of falling, have indicated variable effects among PwPD in other cueing-related studies, particularly where music cueing is not personalised [9,44,73]. The findings from this study will establish a baseline understanding of their (i) validity (from an app and smartphone worn on the lower back) and (ii) whether personalised cues can consistently reduce stride variability across a broader range of participants.

Observed gait responses will be interpreted in the context of sequence-conditional effects (cue order, exposure, and adaptation over time), and not as definitive evidence of causal superiority of one cueing condition over another. Analyses of gait variability and asymmetry will be interpreted cautiously, as these measures typically exhibit greater dispersion and may be underpowered (as sample size of based on gait speed). Emphasis will be placed on estimating effect sizes and examining consistency of responses across conditions, rather than on formal hypothesis testing.

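### Each cue is walked once against one shared baseline walk, so the plan cannot separate individual response, which the abstract sets out to clarify, from walk-to-walk variation

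*Protocol article*

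**What the plan says.** The abstract makes two statements about response. One is that "The protocol characterises beneficial and non-beneficial responses to different cueing strategies". The other is: "By explicitly accounting for individual variability, this protocol aims to clarify for whom and under what conditions auditory cueing is appropriate". The Discussion section on the primary objectives adds the question of "whether personalised cues can consistently reduce stride variability across a broader range of participants", and says that weight will be placed on how consistent responses are across conditions.

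The design is in the walking/gait tasks section. "All walks will be 1-minute in duration", and Walk #1 is the only baseline. The first sequence is "NC, Me, WO1, IM, WO2, and VM"; the other two rotate the cue order, and no sequence repeats a cue. The walking part of each washout is there "to further reset their gait but also to assess whether any carryover effect remains before the next cue begins".

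Under Statistical analysis, "within-participant changes from baseline will be calculated using cue-specific difference scores": percentage change for gait speed and stride length, log-ratio for stride-time CV. Under Adherence to cues and musicality, participants are split at a 5% rise in cadence from baseline, and adherence is also kept as a continuous measure. Gold-MSI scores are compared between the two adherence groups and correlated with adherence and with gait change.

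**The concern.** With one observation per participant per cue, the change score is true response plus the error of one cued walk minus the error of one baseline walk. The planned analyses do not pull these apart:

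- The ANOVA, its non-parametric alternatives, the paired tests and the SRM concern group means.
- The ICC compares the app with the reference device, so it measures device agreement and not repeatability from walk to walk.
- The washout walks are used for reset and carryover only.
- The 5% adherence split is applied to a single difference with no error term.
- The cautions in the Discussion concern cue order and low power for variability and asymmetry. They do not concern walk-to-walk noise in an individual's change.

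What is at stake is any statement drawn from these data about which people cueing suits. Such a statement could rest on differences that chance alone produces, and the plan offers the reader no way to judge how far it does.

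**Working it through.** The plan gives no figure of its own for walk-to-walk variation, so there is none to reproduce. The one input taken from it is the SRM of 0.5 for gait speed (Sample size section), together with N = 60. The sample size built on that SRM is a separate matter and is not used here.

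**1. Upper bound for wrong-direction change on one cue.** Assume that change scores are normal, that everyone has the same true benefit and that all spread is noise. Then P(change ≤ 0) = Φ(−SRM).
- SRM 0.5: Φ(−0.5) = 0.309, and 0.309 × 60 = 18.5 participants.
- SRM 0.8: Φ(−0.8) = 0.212.
- SRM 0.2: Φ(−0.2) = 0.421.

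**2. How far true heterogeneity lowers the false part.** Keep SRM 0.5 and let a fraction f of the change-score variance be real (by simulation). The observed wrong-direction share stays near 31%. The part of it made up of people who truly benefit falls:
- f = 25%: 68%, or 0.31 × 0.68 ≈ 21% of all participants.
- f = 50%: 46%, or 0.31 × 0.46 ≈ 14%.
- f = 75%: 28%, or 0.31 × 0.28 ≈ 9%.

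The documents do not give f; these values are assumptions that show the range.

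**3. Shared baseline and consistency across cues.** With equal noise variance s² in every walk, Var(cue − baseline) = 2s². Two change scores from one participant share the baseline error, so their covariance is s² and their correlation is s²/2s² = 0.5. With no cue effect, improving on all three cues means only that the baseline was the lowest of four exchangeable walks, which has probability 1/4 = 25%. With separate baselines it is (1/2)³ = 12.5%. All three changes share the same sign in 50% of participants, against 25% with separate baselines. Part of any apparent consistency is therefore baseline noise.

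**4. The 5% cadence split.** The walk-to-walk CV of cadence is not given; assume 1% to 5%. The SD of percentage change is about √2 × CV. A participant with no true change is labelled adherent with probability 1 − Φ(5 / (√2 × CV)):
- CV 1%: 0.0%
- CV 2%: 3.9%
- CV 3%: 11.9%
- CV 4%: 18.8%
- CV 5%: 24.0%

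By symmetry, a true +10% is missed equally often. The minimal detectable change is 1.96 × √2 × CV = 2.77 × CV, so the 5% cut lies below it once the CV exceeds 5 / 2.77 ≈ 1.8%. For cadence the problem may thus be negligible or material, depending on a quantity that the trial can estimate.

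**5. What the schedule already offers.** Each participant walks uncued three times (NC, WO1, WO2). With complete data and walk-position means removed, the pooled within-person SD has 60 × 3 − 60 − 2 = 118 degrees of freedom.

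**The case against.** The strongest reply is that no stated analysis labels anyone improved or worsened on gait speed, stride length or stride-time CV. The abstract speaks of responses to cueing strategies, and the objectives at the end of the Introduction do not include identifying individual responders. The study is called exploratory, and the abstract leaves systematic evaluation of heterogeneous response to future work. All of this stands. It limits the point to individual-level statements, but it does not make a confounded quantity estimable.

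Four stronger readings are tempting, and the documents do not support them.

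- A reader might infer that participants will be sorted into responders and non-responders. The only individual split is the 5% cadence cut, and it defines adherence rather than benefit.
- A reader might take 31% as the expected error rate. It is the all-noise extreme, while the abstract itself expects heterogeneous responses.
- A reader might conclude that the conditions under which cueing works cannot be studied at all. The protocol mostly uses that word for cue modality, which varies within participants and is modelled with walk order. Only tempo, loop and setting are fixed.
- A reader might fault the plan for not relating MDS-UPDRS, falls history, FES-I or MoCA to response. Musicality is a pre-specified analysis of who responds. Further moderators are optional and may be left to a fuller document.

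The remedy is also imperfect. WO1 and WO2 follow cued walks, so their spread can include carryover, practice and fatigue.

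**Conclusion.** The point holds in limited form. The abstract's aim of saying whom cueing suits goes beyond what one walk per cue against one shared baseline can support under the stated analyses. Group-mean results are not affected.

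The 31% at SRM 0.5 is an upper bound on false wrong-direction change. It rests on normality, identical true benefit and no real heterogeneity. The 25% against 12.5% comparison rests on equal, independent walk noise and no cue effect. The true noise share is unknown from the documents. It may be small for cadence against a 10% target and larger for gait speed or stride-time CV. This is a low-cost improvement and does not threaten the main comparisons.

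**What to change.** - Estimate the within-person SD, s_w, for each outcome from NC, WO1 and WO2 after removing walk-position means. Work on that outcome's own change scale: percentage for cadence, gait speed and stride length, log for stride-time CV.
- Report any individual improvement or worsening, and the 5% adherence split, against the minimal detectable change of 1.96 × √2 × s_w.
- Report the variance of change minus 2 × s_w² as an exploratory estimate of true response heterogeneity.
- State that the three change scores share one baseline wherever consistency across cues is discussed.
- Keep the abstract's reference to conditions, but limit it to cue modality and order.

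The cost is analysis time and a short text change; no walks or participants are added. The downside should be stated. Removing walk-position means takes out only the average shift. Any remaining carryover, practice or fatigue inflates s_w, which makes individual labels conservative and biases the heterogeneity estimate downward, possibly below zero. The formula also assumes equal noise in cued and uncued walks. A low value must therefore not be read as proof that responses are homogeneous.

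If this is not done, the abstract should drop the individual-level claim about whom cueing suits, apart from the musicality analysis.

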## Introduction

People with a neurological disorder have a heightened fall risk [1] which can increase morbidity and mortality rates [2]. Increased fall risk often equates to a decline in an individual's confidence to perform routine everyday tasks, which increases the likelihood of future falls, perpetuating a cycle of apprehension and susceptibility [3,4]. That leads to many individuals struggling to actively participate in communities, diminishing their quality of life [5,6]. Parkinson's disease (PD) is a progressive neurological disorder and has the fastest-growing incidence rate, with prevalence projected to double over the next 30 years, with 10 million people with PD (PwPD) living worldwide [7,8]. PD adversely impacts mobility and increases fall risk through gait disturbances, with increased stride-to-stride variability being directly related to an increased fall rate [9]. Over 60% of PwPD encounter at least one fall annually, of which 39% report recurrent falls, varying from 4.7 to 67.6 falls/person/year, with an average of 20.8 falls overall [10]. To reduce fall risk, rehabilitation is administered through walking/gait retraining stemming from a gait assessment in a laboratory/lab or clinic [11,12].

Traditional gait assessment to inform retraining stems from a visual analysis of an individual's overall gait pattern, where tacit expertise can help to identify subtle gait disturbances [13]. However, visual observation alone is subjective and creates inconsistencies between assessors [14] as well as within and across assessments [15]. Although lab-based technologies (e.g., instrumented walkways) enable higher-resolution data capture to provide more objective insights [16,17], they are expensive and limited to bespoke settings which prohibits widespread use [18]. Accordingly, delivery of care and related services to those with increased fall risk is restricted [19]. There is a need to decentralise care by adopting pervasive and scalable technologies for assessment and retraining where wearable inertial measurement units (IMUs) have been suggested [20,21] as they have demonstrated effectiveness in quantifying gait characteristics [22–27]. Regardless, wearable IMU systems may still be described as expensive and technically cumbersome, limiting widespread availability [28]. To enable cost-effective and widespread use, contemporary smartphones (routinely equipped with inertial sensors) are a scalable and practical alternative [29,30].

Although smartphones may be equipped with inertial sensors, they also host a plethora of other technologies which could be harnessed within a gait retraining paradigm. For example, smartphones are readily equipped with wireless communication capabilities, cameras, high-resolution displays, and speakers. The latter is key to deliver retraining via auditory cueing, an effective method for achieving significant gait improvements [31,32], compared to alternatives such as treadmill therapy [33–36]. Auditory cueing typically utilises the rhythmic beat of a metronome to assist individuals in maintaining a steady walking pace [37]. Nevertheless, users often find metronomes to be monotonous and tedious, leading to a lack of long-term engagement [38–40]. Alternatively, music cueing offers a more engaging experience, while also exhibiting a positive influence on gait within PwPD [41–43]. However, the routine uptake of music cueing can be limited by a lack of personalisation, where an individual’s condition and music preferences are not considered, potentially leading to suboptimal engagement and efficacy [44]. Therefore, the development of personalised cueing in PwPD to better retrain gait via a scalable smartphone-based gait assessment is necessary to help reduce fall risk [45–47].

This protocol outlines the methodology for examining CuePD, a smartphone application/app that provides near real-time gait assessment to deliver personalised auditory cues for gait retraining in PwPD. It primarily focuses on determining gait improvements from increases in stride length, gait speed, cadence and reductions in gait variability. Secondly, it will determine the validity of the app’s robustness in PwPD, measuring clinically relevant gait characteristics including mean, variability, and asymmetry across temporal, spatial, and spatiotemporal characteristics. Equally, this protocol also aims to assess usability and relationship between a PwPD musicality, i.e., their knowledge, training, and interest in music, and their ability to adhere to auditory cues.

Therefore, the primary objectives of this protocol are to (i) validate gait characteristics from CuePD and (ii) evaluate the effects of personalised auditory cues (metronome beats, instrumental music, and vocal music) to retrain and improve gait in a lab, i.e., increase gait speed, cadence and stride length while reducing gait variability. Our secondary objectives are to assess recruited PwPD and their (a) acceptance and preference of personalised music cues compared to traditional metronome cueing while (b) understanding their ability to adhere to cues due to their musicality.

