### Outcome measures

#### Validation of gait characteristics.

This assesses the validity of CuePD to quantify PwPD gait characteristics against an established gold/reference-standard wearable (Opal). Gait characteristics include the mean, variability and asymmetry of temporal, spatial, and spatiotemporal characteristics (i.e., step time, stride time, stance time, swing time, stride length). Establishing the validity of CuePD in measuring gait characteristics is essential to accurately detect changes before and after cueing and to precisely tailor the administered cues to each individual’s physiological condition.

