#### Impact of cueing.

This examines the ability of different personalised auditory cues to modify/retrain gait in PwPD. By comparing the effects of metronome beats, instrumental music, and vocal music on gait speed, stride-time variability, and stride length, this outcome seeks to identify which auditory cues most effectively enhance gait stability and performance. ${\text{Coefficient of variance of stride}-\text{time }(\text{CV}}_{\text{stride}-\text{time}})$ will be calculated as the standardised measure of the dispersion of stride times. This provides a more reliable measure of stride-time variability and has shown to be a significant indicator of gait instability and an independent predictor of fall risk among older adults and PwPD, underscoring its importance in clinical and rehabilitative settings [73]. Measuring changes in gait will be key to assessing CuePD as a gait retraining tool.

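### Objective (ii) is worded as gait retraining, but the primary cue comparisons estimate only the immediate response during one minute of cued walking

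*Protocol article*

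**What the plan says.** **The claim.** In the Introduction, primary objective (ii) is to "evaluate the effects of personalised auditory cues (metronome beats, instrumental music, and vocal music) to retrain and improve gait in a lab". The same sentence goes on to spell out what is meant: "to retrain and improve gait in a lab, i.e., increase gait speed, cadence and stride length while reducing gait variability". The Abstract states: "Findings from the study will inform the suitability of gait retraining via smartphone-based app technology, personalised to the individual". Under Outcome measures, Impact of cueing, the article adds: "Measuring changes in gait will be key to assessing CuePD as a gait retraining tool".

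**The exposure.** Under Walking/gait tasks, "All walks will be 1-minute in duration in a continuous 25m loop". Walk #1 is uncued and sets the baseline. Walks #2, #4 and #6 each carry one of the three cues, and participants are told to walk to the beat. The article describes no repeated training session and no later visit.

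**The analysis.** The Sample size section powers a comparison of cued with non-cued walking on gait speed. In Statistical analysis, Equations (30) and (31) form each change score from the cued value and the baseline value. The three primary comparisons, one per cueing modality, are tested at 0.0033. Comparisons between modalities and the washout analyses are secondary or exploratory, at 0.05 without multiplicity correction.

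**The washout.** After Walks #2 and #4 a two-part washout "will be implemented to minimise any potential carryover effects from the previous auditory cue". Part 1 is seated backward counting. Part 2 is a measured 1-minute uncued walk, intended both to reset gait and to check for any remaining carryover. Statistical analysis then plans a carryover score, described as a measure of how much of the cue effect persists.

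**The concern.** Retraining, as the article itself uses the word, is more than walking differently while a beat plays. The Introduction treats it as the form in which rehabilitation is delivered to lower fall risk, and the Abstract links it to long-term engagement. A contrast between one minute of paced walking and one minute of unpaced walking cannot show that gait stays changed once the cue stops, nor that practice with the cue changes it.

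What is at stake is the conclusion drawn from a positive primary result. If gait speed rises during the cued walk, the Abstract and Impact of cueing invite the reading that CuePD works as a retraining tool, when the estimate concerns only the response under the cue. Potential limitations and future considerations does not prevent this: it ties the short testing duration to long-term adherence in daily life and does not mention retention of a gait change.

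**Working it through.** **1. What the primary contrast estimates.** For one participant and one cue, write B for the value in Walk #1 (uncued), C for the value in the cued walk, and W for the value in the uncued washout walk that follows.

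- Equation (30), gait speed and stride length: (C − B) / B × 100.
- Equation (31), stride-time CV: log(C + ε) − log(B + ε).
- Powered contrast (Sample size): cued against non-cued gait speed, again C against B.

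W appears in none of these. Each C comes from a single minute with the cue playing, so the estimand is the immediate response to cueing.

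**2. How much uncued post-cue data exist.** The three sequences in Walking/gait tasks have 20 participants each, and a washout follows only the first and second cues:

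| Cue | First (then WO1) | Second (then WO2) | Third (no washout) |
|---|---|---|---|
| Metronome | Sequence 1: 20 | Sequence 3: 20 | Sequence 2: 20 |
| Instrumental | Sequence 2: 20 | Sequence 1: 20 | Sequence 3: 20 |
| Vocal | Sequence 3: 20 | Sequence 2: 20 | Sequence 1: 20 |

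Each cue is followed by an uncued walk in 20 + 20 = 40 of 60 participants. In only 20 of these is it the first cue, so that no earlier cue can contribute. As a check, 60 participants × 2 washout walks = 120 = 3 cues × 40.

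The counting task comes before every one of these walks. Whatever remains in W is what survived a step designed to remove it.

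**3. What the carryover score measures.** Statistical analysis takes the change from baseline to the cued walk and the change from the cued walk to its washout walk, and subtracts the second from the first. Read literally, the cue change is C − B and the washout change is W − C, so

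score = (C − B) − (W − C) = 2C − B − W.

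Put D = C − B, and let a share r of D be retained, so that W = B + rD. Then score = (2 − r)D.

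- Full reversal (r = 0, W = B): score = 2D.
- Full retention (r = 1, W = C): score = D.

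The score shrinks towards D as retention rises, which is the opposite of its stated meaning. Only if the washout change is signed the other way, as C − W, does it become (C − B) − (C − W) = W − B = rD, which is zero with no retention and D with full retention.

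**The case against.** The strongest reply has four parts.

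- *The objective defines its own terms.* It glosses retraining and improvement as the gait changes themselves, and Study design speaks of responses to cues while walking. On that reading objective (ii) matches Equations (30) and (31). This stands as far as it goes: the analysis does address the glossed quantities. It does not justify the Abstract and Impact of cueing, which carry the result over to retraining and to a retraining tool.
- *Post-cue gait is measured.* This stands, and it limits the point. A reader might infer that every outcome is recorded with the cue on, or that the washout walks are treated only as a nuisance. The documents do not support that: WO1 and WO2 are uncued measured walks, and the carryover score is presented as information on retention. The limit set out here applies to the primary analysis.
- *The article is already cautious.* It calls itself exploratory, stresses effect sizes over formal testing, warns against claims that one cue is superior, and defers home use to later work. None of these passages says that retention is untested.
- *Other wording is harmless.* The Validation of gait characteristics section speaks of the need "to accurately detect changes before and after cueing". That sentence explains why measurement accuracy matters and does not define an effect outcome, so nothing is built on it. The Conclusion refers to rehabilitation but does not claim retraining, and needs no edit on this account.

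A reader might also infer that the washout analysis fails for lack of power. The article gives no expected size for a retained effect and tests washout effects at 0.05, outside the corrected threshold, so no such conclusion is drawn.

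**Conclusion.** The concern holds for the primary cue outcomes. They estimate an immediate response during single 1-minute cued walks and do not support the retraining wording in objective (ii), the Abstract and Impact of cueing. The washout walks give at most an exploratory short-term after-effect: they follow a task meant to minimise carryover, cover each cue in 40 of 60 participants (20 as the first cue), and are absent after Walk #6.

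The counts assume the planned 20 participants per sequence and no attrition. The finding on the carryover score assumes that the washout change is signed as washout walk minus cued walk, which is the direction in which the text describes it; with the opposite sign the score would measure retention correctly. No endpoint, sample size or test of the primary comparisons is called into question here.

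**What to change.** 1. In objective (ii), the Abstract and Impact of cueing, replace the retraining statements with *immediate gait response during cueing*.
2. In Potential limitations and future considerations, add that the primary analysis does not test retention or retraining.
3. In Statistical analysis, define the exploratory after-effect as W − B. On the scales already chosen, this means putting the washout value in place of the cue value in Equations (30) and (31). Report it separately for WO1 and WO2, since WO2 follows two cues, and keep its exploratory status.

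The cost is a few sentences and one redefined exploratory score computed from walks already scheduled. No participants, visits or procedures are added. The downside is a narrower claim: a positive result would support cueing as a means of changing gait while the cue plays, and would leave retraining to a study with repeated exposure and a prespecified retention outcome.
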